## Abstract

**Background:**

We do not yet know how to use blood glucose self-monitoring (BGSM) most effectively in the self-management of type 2 diabetes treated with oral medication. Training in monitoring may be most effective in improving glycaemic control and well being when results are linked to behavioural change.

**Methods/design:**

*DiGEM *is a three arm randomised parallel group trial set in UK general practices. A total of 450 patients with type 2 diabetes managed with lifestyle or oral glucose lowering medication are included. The trial compares effectiveness of three strategies for monitoring glycaemic control over 12 months (1) a control group with three monthly HbA1c measurements; interpreted with nurse-practitioner; (2) A self-testing of blood glucose group; interpreted with nurse- practitioner to inform adjustment of medication in addition to 1; (3) A self-monitoring of blood glucose group with personal use of results to interpret results in relation to lifestyle changes in addition to 1 and 2.

The trial has an 80% power at a 5% level of significance to detect a difference in change in the primary outcome, HbA1c of 0.5% between groups, allowing for an attrition rate of 10%. Secondary outcome measures include health service costs, well-being, and the intervention effect in sub-groups defined by duration of diabetes, current management, health status at baseline and co-morbidity. A mediation analysis will explore the extent to which changes in beliefs about self-management of diabetes between experimental groups leads to changes in outcomes in accordance with the Common Sense Model of illness. The study is open and has recruited more than half the target sample. The trial is expected to report in 2007.

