#### Statistical aspects

In the absence of data relating to change in HbA1c we have calculated sample size conservatively based on the absolute level of HbA1c at follow up. We set out to detect a difference in HbA1c of 0.5% between any two groups. At the outset we estimated the SD of HbA1c as 1.5, based on data from the UKPDS. In practice, the SD of baseline HbA1c among the 245 patients recruited in Oxford was 0.9, but we assumed that the SD among additional patients recruited elsewhere could be as high as 1.5. With 205 further patients, the overall SD would be 1.2, and there would be 150 patients in each group (135 allowing for 10% attrition). These numbers would give 93% power to detect a difference of 0.5% in HbA1c between any two trial groups (2-tailed alpha = 0.05). Figure 1 gives estimates of likely numbers in each group and attrition.

We propose to conduct a single analysis of main trial endpoints at the end of the study. The proposed intention to treat analysis will compare mean levels of HbA1c at follow up between the three study groups, with baseline HbA1c as a covariate, using analysis of covariance. Post-hoc t-tests between groups will be conducted in the event of a statistically significant result. Subsequent analysis will include comparing the two intervention groups against the control group.

We will estimate the intervention effect in sub-groups defined by duration of diabetes (above or below median duration), current management (oral hypoglycaemic dugs or dietary management only), health status at baseline (above or below median EQ-5D score) and co-morbidity (presence or absence of diabetes related complications). We will also explore the extent to which the measures of beliefs included in the study can explain changes in behaviour; firstly by comparing mean levels of beliefs e.g. about controllability of diabetes between experimental groups and secondly by a more formal mediation analysis [28]. Within group analyses will be used to determine fidelity to protocol and conformity to the theoretical model, between group analyses will be used to assess impact of the intervention on key variables proposed by the theoretical model. Additional exploratory analysis will include changes in behaviour in relation to perceived threat and changes in perceived thereat from diabetes.

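### The abstract states 80% power and the statistical section 93% for the same 450 patients and 0.5% difference; only 93% follows from the current planning inputs (minor)

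*Protocol article*

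**What the plan says.** **Abstract, Methods/design.** The planned total is given as: "A total of 450 patients with type 2 diabetes managed with lifestyle or oral glucose lowering medication are included". The power statement reads "The trial has an 80% power at a 5% level of significance to detect a difference in change in the primary outcome", and continues "HbA1c of 0.5% between groups, allowing for an attrition rate of 10" per cent. No SD is given there.

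**Methods/design, Statistical aspects.** The target is: "We set out to detect a difference in HbA1c of 0.5% between any two groups". The authors explain that no data on change were available, and that "we have calculated sample size conservatively based on the absolute level of HbA1c at follow up". The SD was taken as 1.5 at the start. It was 0.9 at baseline in the first 245 patients, and is assumed to be as high as 1.5 in the remaining 205. This leads to an overall SD of 1.2, with 150 patients per group, or 135 after 10% attrition. The section concludes: "These numbers would give 93% power to detect a difference of 0.5% in HbA1c between any two trial groups", with "2-tailed alpha = 0.05".

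**The concern.** Both statements are current text in one article. They share the total (450 = 245 + 205), the difference, the 5% level and the attrition, yet they report different powers, and no sentence connects them. The abstract is not worded as a record of the original design. It is in the present tense and reports that more than half the target has been recruited, which matches 245/450 = 54%, the stage at which the SD was revised.

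What is at stake is reporting. The stated chance of missing a true 0.5% difference is 20% in one place and 7% in the other, and the Discussion presents adequate power as a main advance over earlier trials. A reader who sees only the abstract takes away a figure that the article's own calculation does not support.

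**Working it through.** **Inputs, all from Statistical aspects:** difference 0.5; overall SD 1.2; 135 analysed per group (150 × 0.9); two-sided alpha 0.05. The superseded SD is 1.5. The abstract gives the same total, difference and attrition and a 5% level without stating sidedness. A one-sided reading would raise the power, so it cannot explain a lower figure.

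**Formula (normal approximation, two equal groups):** power = Φ(δ / (SD × √(2/n)) − 1.96).

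**Step 1. Reproduce the 93%.**
Standard error = 1.2 × √(2/135) = 0.1461. Then 0.5/0.1461 = 3.423, 3.423 − 1.960 = 1.463, and Φ(1.463) = 92.8%. The two-sample t calculation gives 92.7%. The stated 93% is confirmed.

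**Step 2. Check the rounding of the SD.**
Pooled SD = √((245 × 0.9² + 205 × 1.5²)/450) = √((198.45 + 461.25)/450) = 1.21. With this value the power is about 92%, so rounding the SD to 1.2 is immaterial.

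**Step 3. Look for the 80%.**

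| SD | n per group | Other condition | Power |
|---|---|---|---|
| 1.2 | 135 | none (current plan) | 92.8% |
| 1.2 | 150 | no attrition | 95.0% |
| 1.2 | 135 | Bonferroni, 2 comparisons | 88.1% |
| 1.2 | 135 | Bonferroni, 3 comparisons | 84.8% |
| 1.2 | 135 | three-group F-test, third mean midway | 87.3% |
| 1.2 | 135 | three-group F-test, third mean equal to one extreme | 95.1% |
| 1.5 | 135 | superseded SD | 78.2% (t: 77.9%) |
| 1.5 | 150 | superseded SD, no attrition | 82.3% (t: 82.1%) |

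None of these variants at SD 1.2 gives 80%. The superseded SD brackets it, at 78% and 82%.

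**Step 4. Does the change scale explain it?**
The article gives no SD of change. Assume SD 1.2 at both times and correlation r between baseline and follow-up, so that SD of change = 1.2 × √(2(1 − r)). With 135 per group the power is 68% at r = 0, 80% at r = 0.25, 82% at r = 0.3, 93% at r = 0.5 and 99% at r = 0.7. An unadjusted change score would thus have 80% power only at a correlation of about 0.25. Because the article calls the follow-up calculation conservative, it implies power for change of at least 93%, so the choice of scale does not account for the 80%.

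**The case against.** The strongest reply is that nothing depends on the 80%. Statistical aspects sets out a complete and correct calculation with its SD, group size, endpoint and alpha. The abstract errs on the low side, and the claim of adequate power holds at either figure. All of this stands, and it is why the point is minor. The printed contradiction remains.

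Some stronger readings are tempting, but the documents do not support them:

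- **That the basis of the sample size is unclear.** It is not: Statistical aspects states both the SD and the endpoint.
- **That the abstract is wrong to speak of a difference in change.** Baseline measures and follow up defines the primary outcome as change in HbA1c to 12 months. Under randomisation the expected between-group difference in change equals that in follow-up level, and the planned analysis of covariance with baseline HbA1c estimates the same quantity. The article openly uses the follow-up level as a stand-in, and baseline adjustment cannot increase the residual variance.
- **That 450 was too few under the original assumptions.** At SD 1.5, 80% power would need 142 analysed per group (142/0.9, rounded up, is 158 per group, or 474 in all). But the article never ties 80% to SD 1.5 with 135 completers, and it does not give the original target number.
- **That current power could fall to 78%.** An overall SD of 1.5 would require an SD of √((450 × 2.25 − 245 × 0.81)/205) = 1.99 in the remaining 205 patients. The article's upper assumption for them is 1.5.

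**Conclusion.** The inconsistency is real and minor. The article gives 80% and 93% power for the same patients, difference, significance level and attrition. Only 93% follows from the current inputs: 92.7% at SD 1.2 with 135 per group, about 92% with the pooled SD left unrounded. The abstract therefore understates the current power by about 13 percentage points.

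That the 80% was carried over from the SD of 1.5 is a reasonable inference from the 78% and 82% found at that SD, but the article does not state it. The conclusion rests on the planning SD and attrition as given and concerns a single pairwise comparison at two-sided 5%. A reader might infer that the trial is underpowered or that its size must be revisited; the figures give no support for either.

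**What to change.** Change the power sentence in the abstract in one of two ways:

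1. State 93% power for a 0.5% HbA1c difference in a single pairwise comparison (two-sided 5%), with SD 1.2 and 135 analysed per group after 10% attrition. Add that it was calculated on follow-up HbA1c as a conservative stand-in for change.
2. If the sponsor confirms the origin, label 80% as the approximate original design figure at SD 1.5, and give 93% at SD 1.2 as the updated figure.

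The reference to change as the primary outcome can stay. The cost is one sentence; the sample size, conduct and analysis do not change.

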**Discussion:**

The *DiGEM *intervention and trial design address weaknesses of previous research by use of a sample size with power to detect a clinically significant change in HbA1c, recruitment from a well-characterised primary care population, definition of feasible monitoring and behaviour change strategies based on psychological theory and evidence, and measures along the hypothesised causal path from cognitions to behaviours and disease and well being related outcomes. The trial will provide evidence to support, focus or discourage use of specific BGSM strategies.

## Background

Diabetes is now a major public health problem. The number of people with diabetes is estimated to reach 330 million by 2030 [1]. There is a high burden from the disease: people with diabetes have an increased two to four fold risk of stroke and heart disease compared to the general population, and increased incidence of retinopathy, peripheral nerve damage and renal problems.

There is now strong evidence for the effectiveness of tight glycaemic control in reducing complications among people with diabetes [2]. However, the evidence with which to translate these research findings into guidance for delivery of health care is lacking [3]. In particular, efforts to promote self management of diabetes have shown limited and transient success in improving HbA1c levels [4]. Blood glucose self-monitoring (BGSM) is a technology that is frequently incorporated into self-management interventions, but has only been separately evaluated in a limited number of trials. Despite the lack of evidence, guidance is given both supporting and discouraging the use of BGSM.

BGSM was used to underpin insulin dose adjustment in the Diabetes Control and Complications Trial among people with type 1 diabetes, which clearly demonstrated the efficacy of glycaemic control in reducing diabetic complications. However, neither the rationale for BGSM nor its efficacy or effectiveness among people with type 2 diabetes is clear. Yet BGSM is now widely accepted as part of management of people with type 2 diabetes [5,6], and the costs associated with its use are rising rapidly [7]. Further trials are required to evaluate the benefit and cost-effectiveness of this technology and its place in the self management of people with type 2 diabetes.

### Target population

People with type 2 diabetes are at risk from a range of macrovascular and microvascular diabetic complications. Large trials have confirmed the effectiveness of intensive glycaemic control at reducing these complications [2]. Tight glycaemic control can be achieved through lifestyle change and medications. The target population will comprise the majority of patients on the average practice list with diabetes; we will focus on those patients within 5–10 yrs of diagnosis who are still comparatively healthy, of average age around 55–65 y, and managed on a range of medications and lifestyle advice. The exclusion of those with regular experience of BGSM will be required to avoid randomising them to a group not using meters.

### Limitations of previous research

#### Limited evidence for effectiveness from non randomised studies

A recent qualitative study has suggested that self-monitoring may be an important factor in helping people achieve a better understanding of their condition [8]. However, one study carried out in outpatient and general practitioner clinics in Italy found that increased frequency of monitoring was only associated with improved metabolic control in people able to adjust insulin doses [9]. A population study in the United States also found little relationship between testing frequency and HbA1c value [10]. By contrast, another large study using a cohort design carried out in a group model health maintenance organisation in California has suggested better glycaemic control among type 2 diabetes patients when using a BGSM compared to no use. Although attempts were made to control for differences between groups, the possibility of confounding between attitudes to self-care and use of BGSM cannot be excluded [11].

#### Limitations of and lack of evidence of effectiveness from randomised trials

Three systematic reviews have provided no evidence that self monitoring is effective in improving glycaemic control for people with type 2 diabetes when compared to urine testing and measurement of glycosylated haemoglobin (HbA1c) [12-14]. The majority of trials identified in these reviews have been carried out in small groups of people. Participants were not recruited from representative populations in the community and the strategies for use of the results from BGSM were not clearly defined. Two more recent studies, set both in hospitals and a family practice setting have adopted a more structured approach to relating blood glucose measurements to subsequent management decisions, but both trials have only published an analysis of people adhering to use of BGSM [15,16].

#### Research on mediators of effect not investigated in trials

There are a small number of studies that offer some insight into how BGSM might lead to improved blood glucose control among people with type 2 diabetes. BGSM may be helpful in the titration of therapy by either patients or by practitioners or both, but whether regular monitoring is more effective than periodic measurement of HbA1c is unknown. Evidence from qualitative studies with patients suggests that awareness of fluctuations in blood glucose levels may promote adherence to self-care behaviours, including medication taking, diet and physical activity in selected patients [8,17].

There is increasing work in the area of diabetes self-management that uses psychological theory to guide intervention and measurement of the processes of behaviour change. One approach, the Common Sense Model (CSM) [18], proposes that how people understanding threats to their health in central in determining efforts to minimise these health threats. For instance, if people with type 2 diabetes do not believe that physical activity affects their blood glucose levels, they have little reason to be more active to control their condition. Beliefs about illness can be categorised in terms of whether they relate to symptoms/ identity, cause, consequences, time lines, and control/ cure [18]. In support of the CSM, previous work has shown that beliefs about the consequences and controllability of diabetes, and the perceived effectiveness of treatment [19-21], predict patient adherence to recommended lifestyle management. Further, an intervention with myocardial infarction patients based on the CSM successfully managed to alter unhelpful beliefs, and led to faster return to work and fewer symptoms in the intervention group [23]. Further work using this approach to guide intervention and measures with people with type 2 diabetes may inform understanding of the potential mechanisms through which BGSM may improve health.

### Limitations of previous interventions

#### Technology

The majority of previous trials have used reflectance meters rather than biosensor technology. The older meters required larger quantities of blood and took longer to produce a reading than current systems. Although when used correctly the older meters provided reliable information, in practice their accuracy, usability and so potential impact was limited and may have formed a barrier to their effectiveness without high levels of motivation.

#### Strategy for use of meters

Only one identified randomised trial specified the approach used with patients to support their interpretation of test results [15]. Patients were told that using the meter and keeping records in a diary would provide information that would help them adjust their diet and lifestyle. A defined counselling algorithm was used to help ensure uniformity of delivery, but the extent to which the counselling helped patients relate the results to behaviour change is unclear. However, the impact of the intervention on self-perception, self-reflection and beliefs are not reported. The only published results of the study are from a per-protocol analysis rather than an intention to treat analysis [15]. Therefore, further work in which the intervention includes linking decision making to behaviour change is required.

#### Quality assurance

Previous trials have not specified the efforts made to monitor delivery of interventions. These include both the process of attempting to ensure that participants understand the techniques being used, and that efforts are made to ensure that the intervention is delivered as per protocol, and that there is adequate separation from the comparison groups in the intervention delivery.

### DiGEM Objectives

#### Primary objective

Our primary objective is to determine whether HbA1c is significantly lower in patients with type 2 diabetes allocated to each of two intervention groups (both receiving training in the techniques of blood glucose self-monitoring, but with one additionally receiving training in the interpretation and application of the results to diet, physical activity and medication adherence) compared to patients allocated to a control group (receiving standardised usual care involving intermittent measurement of HbA1c by health professionals).

#### Secondary objectives

Secondary objectives are:

(i) To compare well-being, satisfaction, health service use and economic cost between allocated groups.

(ii) To conduct an exploratory analysis of changes in mean HbA1c between regimens among sub-groups defined by duration of diabetes, current management, self-reported health status and co-morbidity.

(iii) To test how self-monitoring influences beliefs and behaviour using measures chosen on the basis of theoretical models of behaviour change.

## Methods/design

DiGEM is a four-year study with an open, randomised controlled pragmatic parallel group trial design (Figure 1) with sequential recruitment from two centres. The trial is managed from the Department of Primary Health Care, University of Oxford following NHS R&D Health Technology Assessment Programme guidelines. The study protocol was approved by the Oxfordshire B Research Ethics Committee.

**Figure 1 F1:**
[figure not shown]
Consort diagram showing planned study numbers.

The study design is shown in Figure 1. Participants are randomised to three groups consisting of

(i) a control group receiving standardised usual care and three monthly measurement of HbA1c,

(ii) a self-testing group who, in addition to the above, are carrying out blood glucose self testing with the results interpreted by the study nurse,

(iii) a self monitoring group who, in addition to both of the above, are given support in interpreting and applying the results of blood testing to enhance motivation and maintain adherence to diet physical activity and medication regimens.

Following randomisation, patients receive the allocated education and training appropriate for their group, with follow up to maintain the interventions at four, 13, 26, and 39 weeks with a final assessment at 52 weeks.

### Setting and recruitment

Non-insulin using patients with type 2 diabetes have been recruited from general practices in Oxfordshire and are being recruited from South Yorkshire to take part in the study. The 48 recruited practices represent a geographical spread of rural/suburban centres and cover a wide socio-economic range of patients. The mean number of patients recruited in the 24 practices in Oxfordshire was 10.2, standard deviation (SD) 5.6.

Patients suitable for trial inclusion are identified from practice generated computer lists. Eligible patients are sent an invitation to participate signed by their general practitioner accompanied by an information sheet and a reply paid envelope to facilitate response. One further letter is sent if no response is received in one month.

### Study population: inclusion and exclusion criteria

Inclusion criteria are type 2 diabetes, aged 25 years or more at diagnosis, managed with lifestyle or oral hypoglycaemic agents, independent for activities of daily living. Exclusion criteria are use of blood glucose monitor twice a week or more often over the previous three months, current use of insulin, co-morbidity or limited life expectancy that would make intensive glycaemic control inappropriate, last clinic HbA1c or HbA1c at the assessment visit less than 6.2%, or unable to follow trial procedures.

### Randomisation

Participants are randomly allocated to one of the three groups using a partial minimisation procedure to adjust the randomisation probabilities between groups to balance important covariates including duration of diabetes, HbA1c, and prior medication using a computer programme (Minim, ).

